**Allocation + initial assessment**

Assessed for eligibility

>65 years old

Physician on-call thinks that patient is suitable for non-operative treatment

Fracture reduction if necessary

GP´s visit and x-ray prior to cast removal

Mailed Questionnaires, no physician´s visit

PRWE, QuickDash, VAS, 15-D, PCS

**1 +2 week Follow-Up**

Randomization by the ER personnel

**Enrollment**

**5 w follow-up**

**1+2 y Follow-Up**

Allocation to volar flexion & ulnar deviation cast and PCS

GP´s visit + x-ray if seen necessary by the physician on-call

Physician´s visit at study hospital, x-ray

 PRWE, QuickDash, VAS, PCS, 15-D ROM, grip

**3 m Follow-Up**

GP´s visit and x-ray prior to cast removal

Mailed questionnaires, no physician´s visit

 PRWE, QuickDash, VAS, 15-D, PCS

Physician´s visit at study hospital, x-ray

 PRWE, QuickDash, VAS, PCS, 15-D ROM, grip

Excluded

Direct operative treatment

Refuse to participate the study

Open fracture more than Gustilo 1 gradus

Age 64 or less

Chauffeure’s or Barton´s fracture

Smith´s fracture (volar angulation of the fracture)

Does not understand written and spoken guidance in local languages

Pathological fracture or previous fracture in the same wrist, antebrachium or elbow

Pathological fracture or previous fracture in the same upper extremity

Allocation to functional cast and PCS

GP´s visit + x-ray if seen necessary by the physician on-call

Cast immobilization time will be 5 weeks according to current guidelines in Finland. The final physician’s visit will be at the time of the cast removal. All patients have an x-ray prior to cast removal. After cast removal, the decision to refer patient for physiotherapist will be left to discretion of the treating physician.

After three months the patient will visit orthopedic outpatient clinic in the hospital where the treatment was initially started (Table). This visit is part of the study protocol. During the visit a direct lateral and anteroposterior radiographs will be taken. PRWE, PCS, Quick-DASH, 15-D and pain in VAS will be assessed. The number of cast changes during treatment is queried from the patient and the number of changes is recorded.

The 1- and 2-year **follow-ups are executed with postal questionnaires in order to reduce patients’ discomfort and aiming to as easy-as possible handling of the follow-up data. Controls include** PRWE, VAS (for level of pain), PCS, Quick-DASH and 15-D.

At the 1 and 2 year follow-up complications will be recorded from patient records.

|  | **Medical history** | **Radiograph** | **PRWE** | **PCS** | **Pain** | **Grip** | **Quick-DASH** | **15-D** | **VAS** |
| --- | --- | --- | --- | --- | --- | --- | --- | --- | --- |
| **Baseline** | x | X |  | x |  |  |  |  |  |
| **1-2 weeks** | (x) | (x) |  |  |  |  |  |  |  |
| **5-6 weeks** | (x) | X |  |  |  |  |  |  |  |
| **3 months** | x | X | x | x | x | x | x | x | x |
| **1 year** |  |  | x | x | x |  | x | x | x |
| **2 years** |  |  | x | x | x |  | x | x | x |

(x) = taken if required by the treating GP

**Table**: Assessments and procedures of the trial.

- 1. **POWER ANALYSIS**

In this trial, a validated wrist specific PRWE-score is used as the primary outcome measure. Just recently Wallenkamp and coworkers published a report, where minimal clinically important difference in PRWE was set at 11 points with SD of 14 [37]. Based on power calculations (Cl 95%, power 0.95, SD 14) required sample size per group is 40 patients. Assuming 30% of drop-out due to possible surgical interventions during cast treatment, group size would be 52 per group (total 104). In case of patient cross-over, patients will be analyzed according to the intention-to-treat principle.

- 1. **ANALYSIS OF THE MATERIAL**

Each patient will get an initial trial identification number (TIN) which is matched with actual patient identification (ID). **The matching key is stored in study nurse’s office in Tampere University Hospital. Patients are handled only with TIN during follow-up period and analyzing the of the material. Results are given only in general level with mean values thus individual patient’s information is not able to be extracted. The electronical registry contains x-rays and it is located in hospital’s secure server. The research data will be deleted 15 years after the end of the study.**

- 1. **STATISTICAL ANALYSIS**

Continuous skewed variables between the groups were compared by the Mann-Whitney *U* test and t-test is used when variables are unskewed. Results are presented with 95% confidence intervals. Two-way-tables with the chi-square test will be used for dichotomous variables. In subgroup analysis the effect of age, sex, fracture group, smoking, and other diseases will be evaluated against the scores and overall quality of life after fracture.

Analysis of covariance will be used to assess the effect of pain catastrophizing score on the outcome of cast treatment. PRWE will be used as a dependent variable, cast as independent and pain catastrophizing score as covariate.

The effect of cast position and PRWE is investigated also in the multivariate manner. Multivariable analysis is performed with linear regression analysis since the outcome variable PRWE is normally distributed. Main variable of interest included is the cast and age, sex, fracture group, smoking and other diseases are used as confounding variables.

- 1. **ETHICAL ISSUES**

The ethical approval of this study is applied with this research plan.

1. **IMPLEMENTATION**
   1. **CONTINGENCY PLAN**

In Finnish population aged 60 years or more the incidence of DRF can be estimated to be 126-190 per 100 000 person years [38,39]. We need to recruit more than 100 patients as suggested by the power calculation. Time for accrual in a single center is estimated to be too long; therefore to be able to enroll sufficient number of patients we are conducting a multicenter study. This study will be carried in Tampere University hospital, in Central Finland Central hospital and Satakunta Central hospital. Tampere has a catchment area with a population of 300 000 people who in case of an emergency are referred to emergency department located in the Tampere University hospital. The two latters have a catchment area with a population of 100 000 to 150 000 people who are referred to Central Finland and Satakunta Central hospitals in case of an emergency. With the incidence indicated above, we’ll identify 650-950 DRFs among elderly patients aged 60 or more within one year. Therefore we assume to finish recruiting study patients within one year.

We have homogeneity between centers with solid trial designs, data and project management including monitoring. A site personnel training has been carried out. We have been assisted by local research centers. Stability of the trial has been maintained with regular mails where researchers have shared concerns, problems and successes. Regular annual meetings (twice a year, previous on Jan 15, 2016 in Stockholm) will motivate the research team and maintain stable quality in treating. Meetings also include presentations of future studies and trials, methodology and scientific meanings will be debated. Homepage of the research team including current trial (www.nitep.eu) is under coding.

1. **Expected results and impact**
2. We expect to observe better functional outcome after functional cast treatment compared to flexion -ulnar deviation retention cast
3. We expect to observe better grip strength, quality of life, less cast changes and smaller pain in VAS with functional cast compared to flexion-ulnar deviation retention cast
4. Functional outcome is assumed to correlate with PCS regardless of treatment modality
5. After publishing these results we aim to support the creation and dissemination of trustworthy guidelines by health authorities and professional organizations.

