2. to compare pain, disability, quality of life, grip strength, number of complications and cast changes after DRF treated with these two different cast positions
3. to assess the effect of PCS on the functional outcome of conservatively treated DRFs and the possible interaction between PCS and the functional outcome of DRF treatment with two different cast positions
4. **PRIMARY HYPOTHESES**

Our primary null hypotheses are as follows:

1. functional cast position gives similar functional outcome than currently used flexion-ulnar deviation cast position
2. functional cast position yields to similar results to currently used flexion-ulnar deviation cast position with regard to quality of life and grip strength and also with lower rates of complications and number of cast changes during immobilization when treating DRFs.
3. high PCS does not have an interaction with functional outcome on the patient rated wrist evaluation (PRWE) scale after adjusting for cast position used in the conservative treatment
4. **STUDY DESIGN**

The study is a pragmatic, prospective, randomized, controlled, multi-center trial. It is aimed to compare two different positions of a cast. The two cast positions compared are flexion-ulnar deviation position (widely used in Finland) and functional position used in other Nordic countries.

Primary outcome in this study is PRWE score measured after one and two years. Secondary outcomes measured are disability [Quick-DASH (disabilities of the arm, shoulder and arm)], pain in visual analogue scale (VAS), PCS, quality of life (15-D), complications and number of surgical interventions and cast changes. Subgroup analysis will be performed to find out patient specific features indicating good or worse outcome. PCS is used to assess the presence of possible mental susceptibility possibly influencing to the functional outcome.

1. **RESEARCH METHODS AND MATERIAL**
   1. **PATIENT SELECTION**

The eligible study population will consist of all consecutively (aged 65 or more) treated patients with a DRF identified in the public or referral emergency departments of participating hospitals.

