**Following criteria is used in patient selection:**

Inclusion criteria:

- low energy intra- or extra-articular dorsally displaced DRF within 3cm of the radiocarpal joint, diagnosed with lateral and posterior-anterior radiographs in emergency room (ER)
- physician on call (general practician (GP), acute physician, orthopedic resident or orthopaedic consultant) thinks patient could be appropriate for conservative treatment

Exclusion criteria:

- Operative treatment
- Refuse to participate the study
- Open fracture more than Gustilo 1 gradus
- Age 64 or less
- Chauffeure’s or Barton´s fracture
- Smith´s fracture (volar angulation of the fracture)
- Does not understand written and spoken guidance in local languages
- Pathological fracture or (previous) fracture in the same wrist, antebrachium or elbow
  1. **RANDOMISATION**

All patients will be randomized before closed reduction of displaced fractures and immobilization without reduction of non-displaced fractures to either functional cast or flexion-ulnar deviation cast for 5 weeks. Patients will be randomized using a random number matrix in block allocation fashion. The blocks will be stratified by the known associations; age, centre and intra or extra-articular fracture line. The treatment allocations from the matrix will be sealed in envelopes, which are located in the ER. After the patient´s enrollment has been confirmed and informed consent is signed, a medical orderly specialized in casting will open the envelope and make the cast as allocated. The medical orderlies responsible for the casting will not participate in other ways in the study.

The research coordinator will monitor the study flow. An independent monitoring committee has been established.

- 1. **INTERVENTION**

DRFs are in everyday life treated by health care center physicians, experienced acute physicians, and trauma surgeons, thereby; we do not see any reason to limit the number of on call physicians or education or experience of on-call physician in this pragmatic trial.

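### The protocol specifies no masking for whoever measures grip strength at 3 months, although the cast is off by then and masking looks feasible

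*Protocol*

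**What the plan says.** The Study design section describes the trial as follows: "The study is a pragmatic, prospective, randomized, controlled, multi-center trial". Neither that sentence nor any other part of the protocol mentions masking of patients, staff, outcome assessors or analysts.

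On timing, the Follow-up section states: "Cast immobilization time will be 5 weeks according to current guidelines in Finland". The assessment table labels the corresponding row 5-6 weeks. The next study visit is at 3 months: "After three months the patient will visit orthopedic outpatient clinic in the hospital where the treatment was initially started". The flow chart calls it a physician's visit at the study hospital and lists "PRWE, QuickDash, VAS, PCS, 15-D ROM, grip". The running text for the same visit gives a shorter list: "PRWE, PCS, Quick-DASH, 15-D and pain in VAS will be assessed". The table has a grip column, marked at 3 months and at no other time, and no ROM column.

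Two arrangements come near to masking. The Randomisation section says of the staff who open the envelope and apply the cast: "The medical orderlies responsible for the casting will not participate in other ways in the study". The section on analysis of the material has patients handled by trial identification number (TIN) during follow-up.

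The section on expected results gives a direction: "We expect to observe better grip strength, quality of life, less cast changes and smaller pain in VAS with functional cast".

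**The concern.** PRWE, Quick-DASH, VAS and 15-D are self-reports by patients who know how the wrist was held for five weeks. That is unavoidable with this intervention. Grip, and ROM if it is kept, are different. They are effort-dependent measures taken by staff, so knowledge of the arm can enter through the person measuring, and that route can be closed at small cost.

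The conditions for assessor bias are present: a comparison named in the aims, a prediction of its direction, a visit at the treating hospital, and no rule on what the assessor may know. Grip is measured once, so no later measurement can check it, and masking cannot be added after the data are collected. Who assesses an outcome, and with what knowledge, is a matter of trial conduct that belongs in the protocol; it is not something normally left to a statistical analysis plan.

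At stake is how far a difference in grip between the arms, in either direction, can be believed.

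**Working it through.** The protocol contains no figure on this point, so the check is mainly a reading of the sections side by side.

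**1. Is masking of the 3-month assessor specified?** No. The design sentence has no masking term. The exclusion of the casting orderlies removes one group who know the arm, but says nothing about who staffs the outpatient clinic. The TIN rule is pseudonymisation: it hides who the patient is, not which cast was used.

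**2. Would masking be physically possible?** Three months is about 13 weeks. With the cast off at 5 to 6 weeks, it has been off for 13 − 6 = 7 to 13 − 5 = 8 weeks, so the cast no longer reveals the arm. The remaining routes are the treatment record, what the patient says, and the medical history and cast-change questions due at the same visit.

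**3. What is the status of the two measures?**

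| Place in the protocol | Grip | ROM |
|---|---|---|
| Aim 2 and hypothesis 2 | named | absent |
| Secondary outcomes in Study design | absent | absent |
| Flow chart, 3 months | listed | listed |
| Running text, 3 months | absent | absent |
| Assessment table | 3 months only | no column |
| Expected results | better with functional cast | absent |

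The point therefore rests on grip. ROM appears only in the flow chart and is not declared as an outcome.

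**4. How large could the effect be?** The protocol gives no SD for grip or ROM and no estimate of bias, so only an illustration is possible. Assume 40 assessed per group (the per-group number in the power analysis, which was computed for PRWE), a two-sample t-test at two-sided 5%, no true difference, and a systematic assessor shift of *b* SD between the arms.

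- Noncentrality = *b* × √(n/2) = *b* × √20 = 4.472 *b*
- Degrees of freedom = 2 × 40 − 2 = 78; critical value 1.991
- False-positive rate = P(|T| > 1.991), with T noncentral t

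| Assumed shift *b* | Noncentrality | False-positive rate |
|---|---|---|
| 0.1 SD | 0.447 | 0.073 |
| 0.2 SD | 0.894 | 0.143 |
| 0.3 SD | 1.342 | 0.263 |

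With the full 52 per group the same shifts give 0.080, 0.173 and 0.329. A larger sample gives no protection against a systematic shift.

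**The case against.** **The protocol is silent; it does not say that the assessor is unmasked.** This stands. A reader might infer that grip is assessed open-label, but the text does not support that. It supports only that no masking is specified.

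**Several links are inference.** This also stands. The protocol does not say that the clinic record shows the cast position, who measures grip or how, or that this person shares the stated expectation. Clinic staffing is not described, so feasibility with existing staff is plausible but not established.

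**The consequence is limited.** A reader might infer that masked grip would corroborate the primary outcome, or that without it nothing in the trial is protected from expectation. Neither holds. The primary outcome is PRWE at 1 and 2 years, collected by post; grip at 3 months precedes it by 9 to 21 months and cannot directly corroborate it, and assessor masking would not alter it. Radiographs and surgical interventions are not self-reports.

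**The size is assumed.** True. The percentages show what a given shift would do; they are not evidence that a shift occurs in this trial.

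**The change costs more than a sentence.** In part. If one physician takes the history, asks about cast changes and measures grip, the order of the visit must be fixed at three hospitals.

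These objections narrow the point without removing it. Grip is a declared comparison, its direction is predicted, and no provision keeps its assessor unaware of the arm.

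**Conclusion.** The concern holds in a limited form. The protocol specifies no masking for the person measuring grip at 3 months, and neither the separation of the casting orderlies nor the TIN rule supplies it. With the cast off for about 7 to 8 weeks, masking appears feasible.

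One secondary outcome at one time point is exposed, together with ROM if it is retained; the primary analysis is unaffected. The size of any bias cannot be derived from the document. The rates of about 7%, 14% and 26% depend on the assumed shifts, on 40 assessed per group and on a true difference of zero. The change is worth making because it is cheap and cannot be made retrospectively.

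Separately, the sections disagree on whether grip and ROM are outcomes, and this needs to be settled.

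**What to change.** Add to the 3-month visit procedure:

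- Whoever already measures grip (and ROM, if kept) does so first, on a form carrying only the TIN, before opening the treatment record and before the medical history and cast-change questions.
- The patient is asked beforehand not to mention the cast position.
- The form records whether the assessor learned the allocation.
- If a site cannot work this way, the protocol states that grip is assessed unmasked there, and the result is interpreted accordingly.

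In the same edit, reconcile the status of the two measures. Add grip to the secondary outcomes in Study design and to the 3-month running text, in line with aim 2 and the table. Either declare ROM as an outcome in the text and table, or remove it from the flow chart.

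The cost is a short procedural paragraph, one tick-box and a fixed visit order at three hospitals. No additional visit or measurement is needed, and no additional assessor if the existing one can measure before seeing the record. Masking will be incomplete where patients reveal their cast, which is why unmasking is recorded.

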The purpose of conservative treatment is to stabilize the fracture with cast, brace or other external supports where the bone is allowed to heal anatomically. Immobilization should also relieve pain. Several different methods of immobilization have been described [13-18]. Historically most often used method is closed reduction and immobilizing the wrist into slight flexion-ulnar deviation-pronation –position. The flexion -position was first described by Frederic J. Cotton in 1910 [19]. Although the method was commonly used in that era there was growing evidence that a strict wrist flexion could lead to median nerve compression. In 1933 Abbott and Saunders noticed that reduction in flexion increases resistance for dye flow in cadaver carpal tunnels [20]. Later the method was condemned as ‘Cotton-Loder’ position and since then the absolute flexion has been abandoned. Slight flexion-ulnar deviation position was, however, considered to be beneficial for maintaining the fracture reduction during immobilization. It was suggested that in this reduction position the soft tissue envelope around the fracture fragments and the distraction produced by radiocarpal ligaments (ie. ligamentotaxis) could resist the dislocating forces generated over the fracture line. In 1950 Sir John Charnley published his classic and highly influential guideline “The Closed Treatment of Common Fractures” [21]. In his book Charnley described the use of 3-point technique to immobilize the fracture in a slight flexion-ulnar deviation-pronation position. This technique has been widely adopted worldwide by several leading authors in important textbooks of orthopaedics and hand surgery until the recent years.

However, in clinical practice the flexion-ulnar deviation reduction position causes common extensor tendons to be tightened and thereby not allowing proper finger flexion during treatment. This is problematic especially among elderly people in whom degenerative joints are vulnerable to immobilization- induced stiffness. The median nerve compression, the most common complication in DRF, is also been seen n patients with increased carpal tunnel pressure. The pressure has been shown to increase three-fold when changing the neutral cast immobilization position to flexion [22-24].

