Closed reduction is done under local anaesthesia by injecting Lidocaine 1% into fracture area. The technique of closed reduction is not limited to any specific technique. Fluoroscopy can be used when performing closed reduction if it is available in the participating center. Cast reduction position examples are delivered to participating centers to assure correct position of casting. After closed reduction, additional radiographs will be taken to confirm the reduction of the fracture. After physician on-call has accepted the fracture to be treated conservatively, a dorsal splint for 5 weeks is used. Non-displaced fractures are immobilized according to randomization without reduction.

After the allocation and preparing the cast, the patient is asked to fill the PCS questionnaire.

- 1. **FOLLOW-UP**

Follow-up visits are being conducted in primary health care centers as seen necessary by the physician on-call. They are arranged by the regional guidelines, at 1 and 2 weeks with radiographs. Due to the pragmatic nature of the trial we will not set any angulation degrees or shortening limits indicating operative treatment if reduction is lost during the follow-up. Whether the achieved angulation and/or possibly restored shortening is lost during the follow-up, the decision to consult local orthopedist or hand surgeon is left to the discretion of treating physician. Moreover, if patient has been referred for operative treatment from the primary care by the physician on-call but conservative treatment is chosen in the referral center ,the patient is still eligible for the study. Follow-up of these patients is conducted in the primary care or hospital based on local protocols. Since patients will be randomized in blocks by the hospital, we will assume that randomization will take care of the possible differences between centers.

**Figure**: Flow chart of the trial.

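### Complications, a secondary outcome, are captured only by record review at 1 and 2 years; a fixed question set at the existing 3-month visit would be a cheap improvement

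*Protocol*

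**What the plan says.** The Study design section lists among the secondary outcomes "complications and number of surgical interventions and cast changes". Complications are also part of the second objective, and the second hypothesis refers to the functional position "also with lower rates of complications and number of cast changes during immobilization". No definition or list of complications is given.

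The Background discusses two harms linked to immobilisation. It describes "The median nerve compression, the most common complication in DRF" and reports a three-fold rise in carpal tunnel pressure when the cast is moved from neutral to flexion. It also calls the restriction of finger movement in the flexed position "problematic especially among elderly people in whom degenerative joints are vulnerable to immobilization- induced stiffness".

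The Follow-up section contains the only sentence on how complications are collected: "At the 1 and 2 year follow-up complications will be recorded from patient records". The assessment table has no column for them. For the cast weeks the same section says: "Follow-up visits are being conducted in primary health care centers as seen necessary by the physician on-call". The table marks medical history at 1-2 and at 5-6 weeks as taken only if the treating GP requires it.

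At 3 months every patient attends the study hospital. The table marks medical history, radiograph and grip there without the discretionary bracket, and the flow chart adds ROM. The number of cast changes is asked of the patient.

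On oversight, the Randomisation section says: "An independent monitoring committee has been established". Its remit, data and review times are not given. On accrual, the Contingency plan says: "Therefore we assume to finish recruiting study patients within one year".

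**The concern.** The complication comparison is part of a stated hypothesis, and the mechanism set out in the Background acts while the cast is on. The stated capture comes long afterwards and depends on routine notes. A nerve symptom or stiff fingers in week 3 is counted only if three things happen: the patient mentions it, a clinician writes it down, and those notes are among the records later searched. The protocol does not say whether the records searched include primary-care notes.

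Two consequences follow. Incomplete capture shrinks any true difference and leaves fewer events in a comparison that is already small. Unequal capture could bias it, because the treating physicians whose notes form the data can see which cast the patient wears. Either way, a finding of no difference in complications would be hard to interpret if patients were never asked in a standard way.

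**Working it through.** The protocol states no complication rate, capture rate or safety sample size, so there is no figure to reproduce. The check compares the text on timing and source, then gives an illustration on assumed rates.

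**1. Two cast-phase outcomes in hypothesis 2, side by side**

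| | Cast changes | Complications |
|---|---|---|
| Source | Asked of the patient | Patient records |
| When | Described with the 3-month visit | 1 and 2 years |
| Same question in both arms | Yes, a direct query | No query specified |

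The protocol already uses a direct query for one of these outcomes and not for the other.

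**2. Timing against recruitment**

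Inputs: 104 patients (Power analysis), recruitment within one year (Contingency plan), 5-week cast (Follow-up). Uniform accrual over 12 months is an assumption. When recruitment closes:

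- past the 5-week cast: 104 × (52 − 5)/52 = 94 patients
- due or past the 3-month visit: 104 × (12 − 3)/12 = 78 patients
- the first patient reaches the 1-year record review at month 12, just as recruitment closes.

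So 3-month study data would exist for about three quarters of the patients (78/104 = 75%) before recruitment ends, but none of it is designated as complication data.

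**3. Effect of under-capture (illustration only)**

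Let p1 and p2 be true complication rates, c the fraction captured (equal in both arms), and n = 52 per arm with no losses. Observed rates are a = c·p1 and b = c·p2, with mean m = (a + b)/2. For the planned two-sided chi-square test at 5%:

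power ≈ Φ( [ (a − b) − 1.96·√(2m(1 − m)/n) ] / √( [a(1 − a) + b(1 − b)]/n ) )

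For 20% v 10% at full capture: m = 0.15, √(2 × 0.15 × 0.85/52) = 0.0700, √((0.16 + 0.09)/52) = 0.0693, so power = Φ((0.10 − 0.1373)/0.0693) = Φ(−0.54) ≈ 0.30.

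At half capture (10% v 5%): m = 0.075, the two roots are 0.0517 and 0.0514, so power = Φ((0.05 − 0.1012)/0.0514) = Φ(−1.00) ≈ 0.16.

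| Assumed true rates | c = 1 | c = 0.5 | c = 0.25 |
|---|---|---|---|
| 10% v 5% | 0.16 | 0.10 | 0.07 |
| 20% v 10% | 0.30 | 0.16 | 0.10 |
| 30% v 10% | 0.73 | 0.40 | 0.21 |

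Expected events for 20% v 10% are 52 × 0.20 = 10.4 and 52 × 0.10 = 5.2 at full capture, and 5.2 and 2.6 at half.

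**4. Effect of unequal capture (illustration only)**

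With equal true rates of 15% and capture of 70% in one arm and 40% in the other, the observed rates are 0.15 × 0.70 = 10.5% and 0.15 × 0.40 = 6.0%. That is a difference of 4.5 percentage points with no true difference. The 70/40 split is chosen to show the mechanism. Nothing in the protocol indicates its size or direction.

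**The case against.** The strongest reply is that the sentence fixes when complications are extracted, not the period covered. A review at 1 year looks back and can take in the cast weeks, and silence about primary-care notes does not mean they are excluded. The trial is declared pragmatic, and record-based capture suits that. Contact during and after casting is also not wholly discretionary. There is a physician's visit at cast removal with a radiograph for all patients, and the 3-month visit has medical history, radiograph and grip, with ROM in the flow chart. Surgical interventions are listed as a separate outcome, so a complication leading to surgery has a second route to being counted. The Expected results section does not list fewer complications. Even with perfect capture the comparison has low power at most of the assumed rates.

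Much of this stands, and it rules out two stronger readings that a reader might infer. One is that the review will miss most complications. The documents do not support this, because the review is retrospective and no capture rate is given or can be derived. The other is that the monitoring committee would have nothing to look at during recruitment. Its remit is not stated, and 3-month history, radiograph and grip data accrue meanwhile. Nor can it be said that stiffness is never examined, since the flow chart does not say which joints ROM covers.

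What does not fall is the core. An unspecified medical history is not a defined complication assessment, and grip or unspecified ROM does not identify median nerve compression. The pragmatic argument does not reach the 3-month visit, which the protocol itself describes as a study visit, so one more question there leaves routine care unchanged.

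**Conclusion.** The point holds in a limited form. The only stated capture of a hypothesis-level secondary outcome is retrospective record review at 1 and 2 years. The harms that motivate it would arise mainly in a 5-week period of primary-care follow-up in which history is optional. Complications may be under-recorded, to an extent the documents do not allow one to derive, and possibly differently by arm. No complication data are scheduled before year 1.

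The timing result rests on the planned one-year recruitment and uniform accrual. The power and unequal-capture figures rest entirely on assumed rates and show only how the effect works. This is a stated collection method that can be bettered cheaply, not a flaw that undermines the primary PRWE comparison.

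**What to change.** At the existing 3-month study-hospital visit, next to the query on cast changes, add a short fixed checklist asked in the same words in both arms. It should cover median-nerve symptoms since the injury, finger stiffness, any surgery, and any other wrist complication, each with date of onset. Add a complications column to the assessment table.

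Keep the 1- and 2-year record review as a supplement, and state that it covers primary-care as well as hospital records. The 3-month counts by arm can then be made available to the existing monitoring committee while recruitment is open.

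The cost is one page on an existing form, a few minutes per visit and a sentence on record sources, with no extra visit or staff. Consent must cover access to primary-care records. The consent form is not among the documents reviewed, so this needs checking. Patients would be recalling events roughly 8 weeks after cast removal (13 − 5 weeks), so the checklist will not be complete either. It does give a uniform question in both arms, and the record review can fill gaps.
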